### Sample Size

Using data from a previous observational study evaluating one-year statin adherence of new users at 34 different community pharmacies in Saskatchewan [21], we were able to estimate an intracluster (or intraclass) correlation coefficient (ICC) of 0.0143, and determine that mean statin adherence in this population was 0.71 (SD 0.13). Thus, in order to detect a 15% improvement in mean adherence, considered to be clinically important [24,25], 270 subjects would be required in each group to detect a difference of approximately 15% with 80% power at a p < 0.05. The community pharmacies enrolled in CPATCH are expected to accrue a minimum of 25 subjects over a 6 month period. As a result, 22 clusters (pharmacies) are calculated as needed, but 30 will actually be enrolled as the planned statistical analysis requires a minimum of 15 clusters within each group [26].

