### Statistical Methods

Baseline characteristics will be compared between groups using both cluster and individual-level variables (Table 2). To determine the effect of the intervention, mean adherence will be measured at one year using generalized estimating equations (GEE) with an exchangeable correlation matrix and robust standard errors, with individuals as the analytical unit [27]. Both univariate and multivariable models will be developed based on individual and pharmacy-level variables considered statistically significant (P < 0.10), or clinically important (e.g. age, sex) (Table 2). All first order interactions will be tested.

**Table 2 T2:** Individual and Pharmacy Level Variables Available for Multivariable Analysis

Variable	Description	Database Source

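### The model behind the primary p < 0.05 is not fixed: the data choose the covariates, neither model type is named as primary, and all first-order interactions are tested without limit

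*Protocol article*

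**What the plan says.** The Outcomes section of the protocol article names one primary outcome, mean statin adherence measured on individuals. The Sample Size section sets the level: "270 subjects would be required in each group to detect a difference of approximately 15% with 80% power at a p < 0.05".

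The Statistical Methods section first gives the method for the intervention effect: GEE with an exchangeable correlation and robust standard errors, with no covariates listed. It continues: "Both univariate and multivariable models will be developed based on individual and pharmacy-level variables considered statistically significant (P < 0.10". The same sentence opens a second route for variables thought clinically important, with age and sex as examples only, and points to Table 2 as the pool. It ends with: "All first order interactions will be tested".

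The article does not say which of these models yields the primary P value, what the P < 0.10 criterion is tested against, or what status the interaction tests have. The Randomization section says that investigators and participating pharmacies could not be blinded to the assigned group.

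**The concern.** A 5% level describes a procedure that is fixed before the data are seen. Here the adjustment set depends on P values from the trial data and on a judgement about clinical importance whose list is left open. More than one model may be available for the intervention effect, with no ranking between them. The people making these choices know which pharmacies are in which arm.

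Two things are at stake. The first is the primary conclusion, which could depend on which model is put forward. The second is subgroup claims: testing every first-order interaction on a table of this size will readily produce some significant results by chance.

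**Working it through.** **Inputs.** Level 0.05 (taken as two-sided; sidedness is not stated). "intracluster (or intraclass) correlation coefficient (ICC) of 0.0143". Pharmacies are "expected to accrue a minimum of 25 subjects over a 6 month period". "22 clusters (pharmacies) are calculated as needed, but 30 will actually be enrolled". The cluster count reproduces: 270/25 = 10.8, rounded up to 11 per group, and 2 × 11 = 22. How 270 itself was reached is a separate question and does not enter here. Table 2 has 10 individual-level and 5 pharmacy-level rows, 15 in all.

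**Simple bound for two models.** If success could be claimed on either of two tests, each truly at 5%, the error rate is at most 0.05 + 0.05 = 10%, and 1 − 0.95² = 9.75% if they were independent. Two models fitted to the same data are positively correlated, so the rate should be lower.

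**Null simulations** (no intervention effect, ICC 0.0143, 30 pharmacies, two covariates always in, the others kept if P < 0.10 against the outcome):

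- A: 700 trials, mean cluster size 30 (CV 0.5), 8 individual-level and 7 pharmacy-level candidates, all noise.
- B: 8,000 trials, 25 per pharmacy, 10 individual-level and 5 pharmacy-level candidates, some truly prognostic. Linear regression with cluster-robust errors stood in for GEE.

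Type I error, %. Uncorrected means robust errors with a normal critical value; corrected means a small-sample adjustment with a t reference.

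| Test | A uncorrected | A corrected | B uncorrected | B corrected |
|---|---|---|---|---|
| Unadjusted | 6.9 | 4.4 | 6.7 | 5.2 |
| Two fixed covariates | – | – | – | 5.5 |
| Selected at P < 0.10 | 7.4 | 5.0 | 8.3 | 6.8 |
| Either unadjusted or selected | 9.6 | 6.3 | 11.0 | 9.0 |

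Monte Carlo error: in A about 1 point. For example, √(0.063 × 0.937/700) = 0.9 points, so 6.3% has a 95% interval of about 4.5% to 8.1%. In B it is about 0.3 points: √(0.09 × 0.91/8000) = 0.32.

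Three things follow.

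1. The unadjusted test alone is at 6.7% to 6.9% when uncorrected. Part of the 9.6% and 11.0% is therefore the known bias of robust errors with 30 clusters and has nothing to do with model choice.
2. Screening alone adds little. A shows no clear effect (7.4 − 6.9 = 0.5 points, below its Monte Carlo error). B shows 6.8 − 5.5 = 1.3 points after correction.
3. With 200 clusters of 10 in B (3,000 trials, corrected), the unadjusted, fixed and selected models give 5.5%, 5.1% and 5.2%, but either model still gives 7.6%. What persists comes from having two models to choose from.

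**Interactions.** The intervention with each of 15 variables makes 15 tests: expected false positives 15 × 0.05 = 0.75, and chance of at least one 1 − 0.95¹⁵ = 53.7% if independent. All pairs among 16 terms: 16 × 15/2 = 120 tests, expected false positives 120 × 0.05 = 6. In B, at least one of the 15 intervention terms was falsely significant in 66% of trials with 30 clusters and 55% with 200.

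**The case against.** The strongest reply is that this is a condensed article and that ranking models or labelling interactions is commonly left to an analysis plan. The GEE for the intervention effect is stated first and without covariates, so an unadjusted main analysis with adjusted models as follow-up is a fair reading. That stands as far as silence goes, and silence alone would not be a finding. But the article does more than stay silent: it states a data-driven selection rule and an unlimited set of interaction tests. A later plan could repair these only by overriding the published rule.

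Several stronger readings are tempting, and the document does not support them:

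- *That covariates are screened on the outcome.* The criterion is not defined. The paragraph opens with baseline comparisons between groups, so P < 0.10 could refer to imbalance. That would also make the model data-dependent, but the simulations do not cover it.
- *That two rival estimates of the effect must result.* The univariate models may be one-covariate screens feeding a single multivariable model. Then only the selected-model row of the table applies.
- *That P < 0.10 is the only way in.* There is a clinical route, and the candidate pool is listed in Table 2.
- *That the error rate is about 10%.* This uses uncorrected robust errors and assumes success is claimed on either model, which the article nowhere says.
- *That interaction testing inflates the primary test or removes the main effect.* The article says interactions are tested, not that they are kept in the model.
- *That screening pharmacy-level variables mainly picks up chance associations.* Nothing in the document shows this for real variables such as pharmacy type or location. The most that can be said is that 30 pharmacies are an unstable basis for screening.

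**Conclusion.** The point holds in limited form. The primary outcome and level are fixed, but the model that delivers the primary P value is not, and it is to be shaped by trial data in the hands of unblinded investigators. This is true under either reading of the univariate models and either meaning of P < 0.10.

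The size is modest: with small-sample correction, about 5% to 7% for a selected model and about 6% to 9% if either model could carry the claim, against about 5% for one fixed model. These ranges rest on assumed covariate effects, on screening against the outcome, on linear regression standing in for GEE in one simulation, and, for the second range, on an either-model claim that the article does not make. The two simulations differ enough that no single figure should be quoted.

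The 54% for intervention-by-covariate tests assumes independence. It measures the risk of a spurious subgroup finding and should not be added to the main-effect error rate.

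**What to change.** Before the Ministry releases data, write into the plan:

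1. One primary GEE model for mean adherence: the intervention plus a short fixed list of pre-index covariates, such as age and sex, or no covariates. Restricting the list to pre-index variables matters because Table 2 also offers variables measured after the index date, such as hospitalizations during the study.
2. No P < 0.10 rule for entering covariates.
3. The other model (adjusted or unadjusted) reported as supportive, whatever it shows.
4. Interactions limited to a few pre-named intervention-by-subgroup terms, labelled exploratory and kept out of the primary model.

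The cost is a change of wording; recruitment, data extraction and sample size are untouched. The downside is less freedom in building the model, including less scope to adjust for a prognostic variable that was not foreseen. Such a variable can still be examined in a supportive analysis.

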***Individual Level***		

Sex	Sex of subject	Insurance registry

Age	Age of subject at index date (calculated using date of birth)	Insurance registry

Income security benefits	Patient receives income security benefit (a proxy for socioeconomic status)	Prescription drug

Concurrent medications	Concurrent medications use during one year prior to subject's index date, and for the first 6 months of the study observation period.	Prescription Drug
	Beta blockers	
	Angiotensin converting enzyme inhibitors	
	ASA	
	Oral hypoglycemics	

Prior cardiovascular event	Cardiovascular event(s) in one year prior to subject's index date (Based in ICD-10-CA classifications)	Hospital Services
	Myocardial infarction (I21. - I23.)	
	Stroke (all causes) (I60. - I64.)	
	Transient ischemic attack (G45.0)	
	Unstable angina (I20.0)	
	Other ischemic heart disease (I24. - I25.)	
	Revascularization procedures	
	PTCA (1.IJ.50, 1.IJ.57.GQ, 1.IL.35), CABG (1.IJ.76)	
	Coronary Angiography (3.IP.10)	

Study cardiovascular event	Cardiovascular event(s) during study period (Based in ICD-10-CA classifications)	Hospital Services
	Myocardial infarction (I21. - I23.)	
	Stroke (all causes) (I60. - I64.)	
	Transient ischemic attack (G45.0)	
	Unstable angina (I20.0)	
	Other ischemic heart disease (I24. - I25.)	
	Revascularization procedures	
	PTCA (1.IJ.50, 1.IJ.57.GQ, 1.IL.35), CABG (1.IJ.76)	
	Coronary Angiography (3.IP.10)	

Chronic disease score	Chronic disease score (measure of chronic disease status derived from population-based automated pharmacy data) [37]	Prescription Drug

Prior hospitalizations	Number of hospitalizations in one year prior to subject's index date	Hospital Services

Study hospitalizations	Number of hospitalizations during study observation period	Hospital Services

Physician visits	Number of physician visits during and prior to observation	Physician Services

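### Table 2 lets variables measured after the intervention began into the adjusted intervention-effect model, which can bias the adjusted estimate

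*Protocol article*

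**What the plan says.** Everything here is in the protocol article.

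- **Purpose of the model** (Statistical Methods): "To determine the effect of the intervention, mean adherence will be measured at one year using generalized estimating equations (GEE". The working correlation is exchangeable and the variance estimate is robust.
- **How covariates get in** (Statistical Methods): "Both univariate and multivariable models will be developed based on individual and pharmacy-level variables considered statistically significant (P < 0.10), or clinically important". Age and sex are the only examples of clinical importance.
- **The candidate list** (title of Table 2): "Individual and Pharmacy Level Variables Available for Multivariable Analysis".
- **Rows that reach into the study period** (Table 2, individual level):
  - concurrent medications: "Concurrent medications use during one year prior to subject's index date, and for the first 6 months of the study observation period"
  - study cardiovascular event: "Cardiovascular event(s) during study period"
  - study hospitalizations: "Number of hospitalizations during study observation period"
  - physician visits: "Number of physician visits during and prior to observation"

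Under Subjects, each pharmacy's observation period starts two weeks after its training session, and control pharmacies receive matched start dates. Under Follow-up, each subject's records begin one year before the index prescription. No statement limits the multivariable models to pre-index variables.

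**The concern.** Randomisation makes the arms comparable on what was fixed before the intervention. It gives no such protection to variables that arise afterwards. If the intervention changes a covariate, or if adherence changes it, holding that covariate constant removes part of the effect being estimated. It can also open a path through unmeasured causes, such as illness severity, that affect both the covariate and adherence.

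The article itself makes both routes plausible. Under The Intervention, staff commit to acting on barriers such as cost and intolerance, which could alter physician visits and use of other drugs. The Discussion describes non-adherence as predicting poor patient outcomes, so cardiovascular events and hospitalizations during the study may partly follow from the outcome.

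At stake is whether the adjusted estimate still measures the total effect of assigning a pharmacy to the intervention. Where the bias exists, a larger sample does not remove it.

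**Working it through.** **Step 1. Timing of each individual-level row of Table 2.**

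| Row | Before index | During study |
|---|---|---|
| Sex; age; prior cardiovascular event; prior hospitalizations | yes | no |
| Income security benefits; chronic disease score | window not stated | window not stated |
| Concurrent medications | yes (one year) | yes (6 months) |
| Study cardiovascular event | no | yes |
| Study hospitalizations | no | yes |
| Physician visits | yes | yes |

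Four of ten rows carry study-period information. Cardiovascular events and hospitalizations each have a separate prior-year row. Concurrent medications and physician visits put both periods in one row.

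**Step 2. Would the selection rule keep these rows out?** The article does not say which association the P < 0.10 criterion tests. If it is association with adherence, variables that follow from adherence are favoured. If it is a difference between arms, variables changed by the intervention are favoured. Neither reading screens out the rows at issue.

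**Step 3. Illustration A: the covariate is purely a consequence of PDC.** Let T be arm, Y = τT + e the PDC, and M = bY + u the covariate, with e and u independent.

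- Within arm, the slope of Y on M is g = b·var(e) / [b²·var(e) + var(u)].
- The arm difference in M is bτ.
- The coefficient of T adjusted for M is τ - g·bτ = τ(1 - r²), where r² = b²·var(e) / [b²·var(e) + var(u)] is the squared within-arm correlation of M with Y.

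The documents give no r², so the values below are assumed. Sample Size targets a 15% improvement on a mean of 0.71. Read as relative, that is 0.15 × 0.71 = 0.1065. Read as absolute, it is 0.15. Both are shown.

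| r² (assumed) | Shrinkage | From 0.1065 | From 0.15 |
|---|---|---|---|
| 0.05 | 5% | 0.101 | 0.1425 |
| 0.10 | 10% | 0.096 | 0.135 |
| 0.25 | 25% | 0.080 | 0.1125 |

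The last line needs a within-arm correlation of 0.5.

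**Step 4. Illustration B: the intervention shifts the covariate.** Suppose the intervention moves M by a SD, M changes PDC by b per SD, and an unmeasured factor U, where present, loads 0.5 on M and adds 0.03 to PDC per SD. With the total effect set at 0.1065, the bias of the adjusted coefficient is -a(b + 0.03 × 0.5) with U and -ab without it. A linear simulation (n = 400,000, no clustering) agrees:

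| a | b | U | Formula | Simulated bias |
|---|---|---|---|---|
| 0 | any | either | 0 | within ±0.0002 |
| 0.2 | 0 | yes | -0.0030 | -0.0029 |
| 0.2 | 0.02 | no | -0.0040 | -0.0040 |
| 0.2 | 0.05 | yes | -0.0130 | -0.0131 |
| 0.5 | 0.05 | no | -0.0250 | -0.0250 |
| 0.5 | 0.05 | yes | -0.0325 | -0.0324 |

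All values of a, b and U are assumptions. The bias is negative because they were taken as positive. If a and b have opposite signs and U is absent, -ab is positive and the adjusted effect is inflated. With the covariate omitted, the model recovers the total effect (0.106 to 0.107 across runs).

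**The case against.** The strongest reply is that Table 2 is a pool of candidates. A variable enters only if it passes the criterion or is judged important, and the two named examples of importance are both fixed before index. The article also cites Table 2 for the comparison of baseline characteristics, so the study-period rows might be there for description. This stands in part: the article does not commit to adjusting for these variables. But the table is titled for multivariable analysis, the rule as written can admit them, and they are not baseline characteristics.

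Second, univariate models are also planned, and an unadjusted arm comparison is untouched. That is correct. A reader might infer that the trial's primary result is biased or that the randomised comparison is lost. The article does not support this, because it names neither the unadjusted nor the adjusted model as primary.

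Third, the window for concurrent medications is ambiguous. If the observation period is the pharmacy's, as Subjects suggests, a subject indexed after month 6 would have that window wholly before index. This also stands. The row is not post-index for every subject on every reading, although the window still opens after the intervention began at the pharmacy.

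Fourth, Outcomes adjusts PDC for days in hospital. That deals with how PDC is counted. It does not deal with entering hospitalizations as a covariate.

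**Conclusion.** The point holds as a risk built into the stated rule. Table 2 and the selection criterion together permit adjustment for variables that may be consequences of the intervention or of adherence, and nothing in the article prevents it. The adjusted intervention effect can therefore be biased.

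The size and direction cannot be fixed from the documents. The 5% to 25% shrinkage rests on an assumed r² and on the covariate being a pure linear consequence of PDC. The range of 0 to about -0.032 in the second illustration rests on assumed paths. The bias is zero there if the intervention does not shift the covariate.

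Two stronger readings are not supported. One is that the adjustment must pull the effect toward zero, since other signs of the assumed paths would push it the other way. The other is that the pharmacy-level prescription-volume row shares the problem. That row states no measurement window, and the article shows no route by which adherence support would change the number of new statin prescriptions.

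**What to change.** In Statistical Methods, state that covariates in any intervention-effect model are limited to values fixed before the subject's index date, or to fixed pharmacy characteristics. In Table 2:

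- split concurrent medications and physician visits, and allow only their pre-index parts as covariates;
- remove study cardiovascular events and study hospitalizations from the covariate pool, keeping the prior-year rows;
- report the study-period variables descriptively only.

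Also state whether the unadjusted or the adjusted model gives the primary estimate.

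The cost is small. It is a wording change, with no new data: records are already drawn from one year before index, and the prior-year rows for events and hospitalizations already exist.

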***Pharmacy Level***		

Pharmacy Type	Indicates the type of pharmacy (mass merchandise, chain/grocery, independent) [38]	Investigators to categorize

Pharmacy Location	Rural (population < 10,000)	Investigators to categorize
	Regional (population 10,000 - 100,000)	
	Urban (population > 100,000)	

Prescription Volume	Mean number of new statin prescriptions filled monthly (proxy measure for prescription volume)	Prescription Drug

Pharmacist Coverage	Pharmacist overlap or single pharmacist	Pharmacy survey

Technician Support	Pharmacy technician support	Pharmacy survey

Two secondary endpoints, the proportion of new statin users who exhibit optimal adherence (≥80%) at one-year and mean persistence will be measured on an individual level and analyzed using GEE with an exchangeable correlation matrix and robust standard errors. All analyses will be intention-to-treat, and will include any pharmacies that have withdrawn, as well as any individual subjects who are no longer beneficiaries of the Saskatchewan Drug Plan (due to death or coverage termination). Mean imputation will be used for subjects or pharmacies lost-to-follow-up.

Ethics approval for the study protocol was obtained from the University of Saskatchewan Biomedical Ethics Board (09-135). The study is registered at ClinicalTrials.gov no. NCT00971412.

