### Follow-up

All patient information and outcome data will be collected from administrative databases maintained by the Saskatchewan Ministry of Health (Sask Heath). Sask Health maintains a registry and several databases containing health-services records such as prescription drug data, hospital services data, and physician services data (Table 1). Health services information captured by distinct databases can be linked at the patient level through a unique identification number for each individual. These databases have served as the basis for many observational studies because they capture data on the vast majority of Saskatchewan residents [15-18]. For this study, the databases will be used to capture health services utilization (prescriptions, physician visits and hospitalizations) including diagnoses on all eligible subjects.

**Table 1 T1:** Relevant Data Elements Available from Saskatchewan Health Databases [18]

Database	Available Data
Prescription Drug	Patient information
	Drug information
	Prescriber information
	Dispensing pharmacy information
	Cost information

Hospital Services	Patient information
	Diagnostic and procedure information (based on ICD-10-CA^a ^and CCI^b^)
	Admission and discharge dates
	Length of hospital stay

Physician Services	Patient information
	Physician information
	Diagnostic information (3 digit ICD-9^c ^code)
	Billing information

Insurance registry	Beneficiary information (effective date, end date, sex, age, residence)

a. International Statistical Classification of Disease and Related Health Problems, Tenth Revision, Canada [35]

b. Canadian Classification of Health Interventions [36]

c. International Classification of Disease, Ninth Revision

All Saskatchewan residents are eligible for provincial health insurance coverage, except inmates of federal penitentiaries and members of the Royal Canadian Mounted Police and Canadian Forces (less than 1% of the Saskatchewan population). All health insurance beneficiaries are eligible for Saskatchewan Drug Plan benefits except those who receive these benefits from another government agency, primarily registered Indians (about 9% of the population). Therefore about 10% of the Saskatchewan population is ineligible for the study because of no or incomplete capture of health services information.

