The researchers will provide Sask Health with the list of participating pharmacies and their specific Saskatchewan Drug Plan identifiers (i.e., provider identifier), and enrolment dates. Sask Health personnel will extract all statin prescriptions dispensed from the participating pharmacies during the 18 months following the pharmacy's enrolment date. The individuals receiving these prescriptions will form the pool of potential new statin-users. The prescription histories of the potential pool members will be reviewed to determine which subjects are new statin-users. Hospital, physician and prescription information for eligible new statin-users will be compiled and de-identified prior to release to the researchers for analysis.

It is estimated that each pharmacy will need six months to accrue their sample size of new statin users, thereby allowing 12 months for follow up. However, because it will not be possible to determine when each pharmacy's sample size has been met, data will be collected on all new-users presenting to each pharmacy throughout the observation period. Subjects will be followed from one year prior to their index prescription until the end of the pharmacy's observation period, death, or loss of beneficiary status, whichever is sooner.

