### Outcomes

Although community pharmacies are the unit of randomization, our primary outcome is the mean statin adherence among all eligible new users of statin medications who have been followed up for at least 6 months past their index prescription. This primary outcome will be measured at the individual level. All statin dispensations for each subject will be captured by the prescription drug plan database and mean adherence will be measured using the proportion of days covered (PDC) [19,20], adjusted for any days that a subject may be hospitalized during the observation period. The PDC is calculated by taking the sum of the days' supply for all statin prescription fills during the study period, divided by the number of days of observation. Study participants who have statin dispensations from non-study pharmacies will be captured and accounted for using methods previously published [21]. Secondary outcomes include the proportion of new statin users who exhibit adherence (PDC) ≥80%, and the persistence with statin use among patients with a minimum of 12 months of follow up. Persistence is defined as the number of days from the index prescription to the earliest occurrence of study end date or date of discontinuation (assumed when a refill is not obtained within 102 days of finishing the estimated supply) [22,23]. Only those subjects with a minimum of 6 months of follow-up will be included in the secondary analyses.

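### Single mean imputation for subjects or pharmacies lost to follow-up distorts the standard error or the effect, is largely unnecessary with Ministry data, and leaves subjects lost before 6 months both excluded and included

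*Protocol article*

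**What the plan says.** All references are to the protocol article.

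- **Statistical Methods** (text after Table 2) declares every analysis intention-to-treat. The analyses "will include any pharmacies that have withdrawn, as well as any individual subjects who are no longer beneficiaries", the reason given for the latter being death or termination of coverage. The next sentence fixes the missing-data rule: "Mean imputation will be used for subjects or pharmacies lost-to-follow-up". Neither the mean to be used (arm, overall or pharmacy) nor the meaning of lost to follow-up is given.
- **Follow-up** gives the data source: "All patient information and outcome data will be collected from administrative databases maintained by the Saskatchewan Ministry of Health". Statin dispensing is extracted for 18 months after each participating pharmacy's enrolment date. Subjects are followed "until the end of the pharmacy's observation period, death, or loss of beneficiary status, whichever is sooner".
- **Outcomes** defines PDC as days' supply "divided by the number of days of observation" and says that fills at non-study pharmacies are captured. The primary outcome covers new users "who have been followed up for at least 6 months past their index prescription". For the rest: "Only those subjects with a minimum of 6 months of follow-up will be included in the secondary analyses".

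**The concern.** Replacing a missing outcome with a mean adds a value that carries no variation and then counts it as a real observation. What goes wrong depends on the mean chosen, and the article leaves that open. Own-arm means make the treatment comparison look more precise than it is. An overall mean pulls the arms together.

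The rule also appears to solve a problem that this design mostly does not have. Outcomes come from the Ministry, not from the pharmacies, and PDC has a denominator that stops when observation stops. Finally, two sections describe different analysis sets for subjects who die or lose coverage early. At stake are the validity of the primary test or the size of the primary estimate, the PDC ≥80% endpoint, and which subjects are analysed.

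**Working it through.** The plan gives no loss rate and no figure for the effect of imputation, so there is nothing of its own to reproduce here. f, the fraction imputed, is assumed equal in both arms, with losses at random.

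**Inputs.** From Sample Size: mean 0.71, SD 0.13, ICC 0.0143, 25 subjects per pharmacy, 15 pharmacies per arm, 15% improvement. Read as relative, the improvement is 0.15 × 0.71 = 0.1065, giving 0.8165 in the intervention arm. Read as absolute, that arm is at 0.86. A two-sided 5% level is assumed.

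**Subjects imputed at their own arm's mean.** The completed data have variance (1 - f)s² on N subjects, so the reported SE is s·√((1 - f)/N). The correct SE is s/√((1 - f)N). The ratio is 1 - f, and the true error is 2·(1 - Φ(1.96·(1 - f))).

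| Assumed f | SE ratio | True error |
|---|---|---|
| 5% | 0.95 | 6.3% |
| 10% | 0.90 | 7.8% |
| 20% | 0.80 | 11.7% |

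A cluster simulation (inputs above, cluster-robust SE, t with 28 df, 6000 null runs) asked whether the planned robust standard errors repair this. They do not: the error was 7.2%, 11.4% and 16.6% at f = 10%, 20% and 30%. With observed data only it was 4.8% to 5.4% across all scenarios. The simulation compared arm means directly, a close stand-in for exchangeable GEE at this ICC with equal cluster sizes.

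**Subjects imputed at the overall mean.** The expected difference is multiplied by (1 - f). At f = 10%, 0.1065 becomes 0.0959. In the simulation a true 0.030 was estimated as 0.027, 0.024 and 0.021 at f = 10%, 20% and 30%. Type I error stayed near 5%, and at f = 10% the rejection rate under the true effect hardly moved (71.1% against 71.6% with observed data only). The damage is to the estimate and its interval, not to the test.

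**One whole pharmacy of 15 imputed at its arm mean.** In cluster-variance units that arm's reported variance is (13/14)/15 and the correct one is 1/14. For the difference between arms:
- reported: (13/14)/15 + 1/15 = 0.1286
- correct: 1/14 + 1/15 = 0.1381
- SE ratio: √(0.1286/0.1381) = 0.965, an understatement of about 3.5%
- true error: 2·(1 - Φ(1.96 × 0.965)) ≈ 5.9%

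In the simulation, with two or three pharmacies imputed in each arm, the error was 9.6% and 11.8%.

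**PDC ≥80% endpoint.** If an imputed mean PDC is then cut at 80%, all imputed subjects in an arm fall on the same side. At own-arm planned means, every imputed control (0.71) fails and every imputed intervention subject (0.8165 or 0.86) passes. At the overall mean with equal arms, (0.71 + 0.8165)/2 = 0.763 or (0.71 + 0.86)/2 = 0.785, so all fail.

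**What is actually missing.**
- *Withdrawn pharmacy:* the Ministry extraction covers participating pharmacies for 18 months and captures fills elsewhere, so its patients' outcomes remain available.
- *Subject who dies or loses coverage:* PDC to that date is observed. Fills after loss of coverage are not held.

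**Analysis set.** A subject lost at month 4 fails the 6-month condition in Outcomes but is among those Statistical Methods says are included. A subject lost at month 9 satisfies both and has an observed PDC. The conflict is confined to losses before 6 months.

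**The case against.** The best defence is that the rule will hardly ever be used. If the Ministry data are as complete as described, f is close to zero and so is the harm; even at f = 5% the error is 6.3%. This stands as a limit on size. A reader might infer from the table that the trial's error rate will be 8% to 12%; the documents do not support that, because they give no loss rate.

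Second, the article does not say that held data will be overwritten. It first includes withdrawn pharmacies and only then speaks of units lost to follow-up, so withdrawn pharmacies could be analysed on observed data. That reading is possible. But the imputation sentence names pharmacies as units to impute, and it is hard to see what else a lost pharmacy could be in this design. The text needs to be made unambiguous.

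Third, a reader might infer that every imputed subject would be counted as non-adherent because the planning mean is 0.71. That does not follow: 0.71 comes from the earlier observational study, and under own-arm means at the planned effect the imputed intervention subjects would pass. Nor does the article say that the mean PDC is imputed and then dichotomised, so the distortion is conditional on that.

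Fourth, a reader might take the whole 6-month rule to be a breach of intention-to-treat. New users enter throughout the observation period, so the rule mainly removes late index dates, which is an administrative exclusion. Only exclusion for death or loss of coverage before 6 months conflicts with the intention-to-treat statement.

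Leaving the choice of mean to a fuller document would be acceptable in an article. It does not rescue the rule, since both the arm mean and the overall mean do harm.

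**Conclusion.** The point holds within those limits. The article fixes a method that understates the SE by about the fraction f (own-arm mean) or dilutes the effect by the same fraction (overall mean), and robust standard errors do not correct the former. For a single imputed pharmacy the understatement is about 3.5% for the between-arm SE. A one-arm calculation gives √((13/14)·(14/15)) = 0.931, about 7%, but that is not the quantity tested. All these sizes rest on assumed loss rates, equal loss in the two arms and loss at random.

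The rule brings no offsetting gain: with little loss it adds nothing, and with more it distorts. The contradiction over subjects lost before 6 months does not depend on f and needs resolving in any case.

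**What to change.** 1. Delete mean imputation.
2. State that withdrawn pharmacies are analysed in their randomised arm on their actual dispensing records.
3. For subjects who die or lose coverage, use the observed PDC over days at risk up to that date.
4. Give one inclusion rule that reconciles Outcomes with Statistical Methods, preferably by potential follow-up: index date at least 6 months before the pharmacy's administrative end date. With an 18-month window this means index dates in the first 12 months.
5. Add a sensitivity analysis that excludes subjects with under 6 months of achieved follow-up, or that uses multiple imputation respecting clustering.

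The cost is revised wording and modest programming, with no new data. There is one real drawback. PDC from very short follow-up is biased toward 1, not merely noisy: someone who dies within the supply of the first fill is fully covered for every day observed. Item 4 brings such subjects into the primary set and so changes slightly the population that Outcomes now describes. Item 5 shows whether that matters.
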